### Data analysis

Figure 3 presents the conceptual model that guides our analysis. The model posits, first and foremost, that by 12 months’ implementation and service outcomes will reflect what should be seen in participants if the implementation is properly done, based on previous studies [2, 19, 40]. It also indicates that factors at community (e.g., % poverty), provider (e.g., attitudes to evidence-based practices), and participant (e.g., socio-demographics) levels could moderate the effect of OTCH on implementation and service outcomes. The model also posits that the effect of OTCH vs FEP Usual Care on clinical outcomes (symptoms, functioning, and recovery orientation) will be evident at 24 months. It further proposes that 12-month implementation and service outcomes will mediate 24-month clinical outcomes.

**Fig. 3 Fig3:**
[figure not shown]
Conceptual model for analysis

We will carry out all analyses on an Intention-to-treat basis. All tests will be two-sided with critical value *α*=0.05. Prior to analysis, we will examine all variables for outliers and inconsistencies and examine their distributions. The distributions of all continuous variables will be checked for normality, and transformations will be employed to normalize distributions, if necessary, before applying specific parametric techniques. Missing data will be imputed, using multiple imputation procedures in standard statistical software (e.g., Stata or SAS).

#### Aim 1a and Aim 1b analyses

We have selected 3 measures of implementation (fidelity, acceptability, and uptake) and 3 measures of service outcomes (patient-centeredness, adherence, and retention) that represent the active ingredients of CSC for people with FEP. These six measures reflect care processes that will be fundamental to the implementation of the OTCH program [13]. Tests for treatment differences between the intervention arms on each of the six outcomes will be performed using a hierarchical linear model (HLM) for each outcome including clinic-level random effects to account for clustering of participants within clinics and participant-level random effects to account for repeated measures on the same user over time. The primary fixed effects will be an indicator for intervention status (OTCH, FEP Usual Care), time (12 or 24 months), and intervention*time. The magnitude and statistical significance of the beta coefficients from the HLMs will be used to test whether implementation and service outcomes differ between intervention arms at 12 and 24 months. If descriptive analyses identify any baseline differences between randomized groups of participants at baseline, we will consider adding the respective covariate to the model to adjust for this.

We will examine multilevel factors that may moderate the implementation of OTCH (see Table 1). (1) *Community level*: there is evidence that access to and engagement with mental health services is low among those who reside in poor communities [41]. (2) *Provider level*: we hypothesize that more positive attitudes toward evidence-based practices and recovery orientation will be associated with more successful implementation of programs which have these characteristics like OTCH [42]. (3) *Participant level*: we also hypothesize that socio-demographics and baseline clinical state will be predictors of implementation and service outcomes based on prior studies with clinical outcomes [17]. We will test this aim by including all three types of moderators into the HLM utilized for Aim 1.a. Specifically, because we aim to test whether these factors differentially affect the implementation of the OTCH compared to FEP usual care (i.e., an interaction with treatment), we will incorporate a random intervention effect into the HLM and allow the factors to predict the random intervention effect at both the clinic and participant level. The magnitude and statistical significance of the beta coefficients for these factors will provide the test of them as treatment effect moderators.

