For the cluster trial, power was calculated conservatively based on the participation of 270 participants (rather than the full 300 to be enrolled), anticipating a possible participant drop-out of ~10%. We estimated that, with at least 10 clinics in each condition, we will have 80% power to detect a difference in mean outcomes between study conditions with a moderate effect size of Cohen’s *d* = 0.35 following the standard detectible effect size formula for clustered randomized trials [15, 16]. This power calculation was derived assuming an intra-class correlation of 0.05 for outcomes by clinic (15 participants nested within 21 clinics). We also assume an alpha of 0.05 and that all tests are 2-tailed. Previous research has shown interventions like OTCH to have moderate to large effects on implementation and service outcomes, such as medication adherence, service utilization, and engagement in treatment [5, 17]. We have also shown that FEP providers in Chile rely primarily upon medication and are usually not trained to promote shared decision-making, recovery orientation, or person-centered care [9]. Then it is reasonable to anticipate at least moderate (and probably large) effects of OTCH on these indicators of implementation. Finally, evidence for the expected effect on participant-level symptoms and functioning comes from the RAISE Connection Program study, which indicated improvement over 24 months for participants enrolled (e.g., PANSS improvement effect size 0.91, occupational functioning 1.2, and social functioning 0.72) [17]. Power to detect mediation effects (Aim 2b) depends on the size of the effect of intervention on implementation and service outcomes (path a), and the correlation between implementation and services outcomes and participant level symptoms, functioning, and recovery (path b). Based on tabulated recommendations for sample sizes needed to test mediation effects with a sample of size *N*=270 with follow-up data, we have over 80% power to detect a significant mediation effect with path a=.26 and b=.26. Path a is expected to be >0.35 (argued for Aim 1 above), and we expect based on our previous work that there will be at least moderate associations between implementation and clinical outcomes (*r*>0.40), assuming no confounding of mediator-outcome relationship.

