		Providers and participants	The *Recovery Self-Assessment (RSA)* [24] provider and patient versions is a 32-item, self-administered rating scale that focuses on perceptions of recovery principles and overall quality of services. It captures both providers’ and patients’ perceptions that a specific recovery-oriented intervention, in this case OTCH, is agreeable, palatable or satisfactory. Each item is rated on a 5-point scale (1 = Strongly Disagree; 5 = Strongly agree). Higher scores indicating greater quality care. Range: 32–160 points.	Baseline, 12, 24 months	15 min
		Providers and partcipants	Ten ad-hoc questions regarding receipt of services that are central to OTCH including supported employment-education, family intervention/support, psychosocial interventions, and personal strenghts and resiliency training	Baseline, 12, 24 months	3 min
Service outcomes	Patient-centeredness	Participants	The *Youth Services Survey (YSS)* [25] is a scale that assesses perceptions about accessibility, quality, and impact of mental health service over a period of time. Only the first 15 items will be used in this study. Each item is rated on a 5-point scale from 1= “Strongly disagree” to 5 = “Strongly agree” (Range: 15–75 points).	Baseline, 12, 24 months	10 min
	Medication adherence	Participants	Measured by the *Brief Adherence Rating Scale (BARS)* [26] It consists of 4 items: 3 questions and an overall visual analog rating scale to assess the percentage of antipsychotic medication doses taken by the user in the past month (0–100%).	Baseline, 12, 24 months	5 min
	Retention	Participants	Time remaining in treatment will be estimated by counting the number of days between randomization to the time of the last mental health service received as defined by the RAISE-ETP report. The *Service Utilization and Resources Form for Schizophrenia (SURF)* [27] will be used to record users’ utilization of psychiatric and psychosocial rehabilitation services by conducting telephone contacts on a three-monthly basis. Range: from 0 to 365 days over a 12-month period; from 0 to 730 days over a 24-month period.	Every 3 months	15 min

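### Retention is one day count cut off at 365 and 730 days; in the shared linear model, read in the usual way, its 24-month test is too liberal and its 12-month test far too conservative

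*Protocol article*

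**What the plan says.** Table 4 of the protocol article defines retention as the days from randomization to the participant's last mental health contact and gives it two scales: "Range: from 0 to 365 days over a 12-month period; from 0 to 730 days over a 24-month period". The two values share an origin and differ only in where the count stops.

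The section on Aim 1a and 1b analyses assigns all six primary outcomes, retention included, to a hierarchical linear model (HLM). The model has clinic-level random effects for clustering and "participant-level random effects to account for repeated measures on the same user over time". Its fixed part is given as: "The primary fixed effects will be an indicator for intervention status (OTCH, FEP Usual Care), time (12 or 24 months), and intervention*time". The coefficients are used to test the arms at 12 and at 24 months. No exception is made for retention. The general data analysis text allows normalizing transformations where needed and sets a two-sided 5% level.

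**The concern.** If T is the time to last contact, retention is min(T, 365) at 12 months and min(T, 730) at 24 months. The second value contains the first, and its possible range is twice as wide, so the two cannot be expected to share a variance. A model with one variance for both times averages a small and a large one. The resulting standard error is too small at 24 months and too large at 12 months.

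At stake are a false retention benefit at 24 months declared more often than the plan allows, and a real benefit at 12 months missed. The second matters because the article's conceptual model expects service outcomes to show by 12 months.

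The interaction also needs care in reading. Suppose, purely for illustration, that the arms differ by 10 percentage points in those out of care by month 12 and nobody leaves afterwards. The day difference still grows by 0.10 × 365 = 36.5 days by month 24.

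**Working it through.** **Inputs from the article.** 21 clinics (10 and 11 per arm in the check); 270 analysed participants, so 270/21 = 12.9, taken as 13 per clinic; two-sided alpha 0.05; the retention definition and the HLM as above. **Assumed**, because the article gives no retention curve and no standard deviation (SD) for retention: Weibull times fixed by the share still in care at 12 and 24 months, and, where stated, lognormal variation between clinics in the hazard of leaving (SD 0.45).

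**The plan's own figure.** The article gives no power or error rate for retention. Its general claim is "80% power to detect a difference in mean outcomes between study conditions" at a "moderate effect size of Cohen’s *d* = 0.35". With 135 per arm, 13.5 per clinic and an intra-class correlation (ICC) of 0.05, the design effect is 1 + 12.5 × 0.05 = 1.625. The effective n is 135/1.625 = 83.1 per arm, and 0.35 × √(83.1/2) − 1.96 = 0.30, which is about 62% power rather than 80%. That is a separate matter and does not enter the argument here.

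**Step 1: pooled variance.** With random intercepts, a common residual variance and complete pairs, the model's variance at each time is v = (v12 + v24)/2. Ignoring clinic effects:

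- real error at 24 months = 2[1 − Φ(1.96 √(v/v24))]
- real error at 12 months = 2[1 − Φ(1.96 √(v/v12))]
- 12-month power, where a correct test has 80% = 1 − Φ(1.96 √(v/v12) − 2.80)

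**Worked case, 80% in care at 12 months and 60% at 24.** The SDs are 82.8 and 219.4 days (ratio 2.65), so the pooled SD is √((82.8² + 219.4²)/2) = 165.8.

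- 24 months: 1.96 × 165.8/219.4 = 1.48, error 13.9%.
- 12 months: 1.96 × 165.8/82.8 = 3.92, error about 0.01%.
- 12-month power: 1 − Φ(3.92 − 2.80) = 13%.

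**Step 2: other curves, raw days.**

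| In care at 12 / 24 months | SD at 12 / 24 months (days) | Error at 24 months | 12-month power (80% if correct) |
|---|---|---|---|
| 95 / 90% | 46 / 128 | 14.1% | 10% |
| 90 / 70% | 50 / 164 | 14.8% | 2% |
| 80 / 60% | 83 / 219 | 13.9% | 13% |
| 60 / 50% | 147 / 308 | 12.5% | 34% |
| 50 / 25% | 126 / 260 | 12.4% | 35% |

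At an extreme 30/10% the error is 11% and the power 51%. From pooling alone the error cannot exceed 2[1 − Φ(1.96/√2)] = 16.6%.

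**Step 3: simulation of 21 clinics × 13.**

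- Without clinic differences, the 24-month error is about 10–11% (t, 19 df) or 11–13% (z).
- With clinic differences it is about 12.5–15% (t) or 15–18% (z). 1,360 actual mixed-model fits at 80/60% gave 16.4% (z).
- The 12-month error is about 0–0.4% throughout.
- With 25–50% out of care by month 24 and the hazard of leaving halved by OTCH, 12-month power is 0.1–7%, against 29–54% when 12 months is analysed alone.
- Separate analyses per horizon reject 4–6% under the null.

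**Step 4: can the article's wording rescue it?**

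- *Transformation.* After log(days + 1) the variance ratio falls to 1.3–2.9 and the 24-month error to 7–11%. A 12-month power of 80% falls to 52–75%. The point masses at the two caps remain.
- *Flexible participant effects.* With a fully unstructured participant covariance and a clinic intercept, 12-month power recovers. The 24-month error is still 8–13% (t), because the variance between clinics also grows with the window.
- *Interaction.* Its test is sound under unequal participant variances alone (4.5–5.2%), but reaches 11–20% when clinics differ in retention and clinic-by-time variance is not modelled.

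**The case against.** The strongest reply is that the article never states random intercepts only or an equal residual variance. It speaks of random effects in the plural at both levels. A participant intercept with a slope fits the wording, and covariance structure is commonly left to a statistical analysis plan, which is not at hand. This stands in part. A reader might infer that the plan forces equal variances; the text does not say so, and the figures in steps 1 to 3 hold only under the usual reading. What the article does fix is the model class and the two tests for this outcome. Step 4 shows that the most natural flexible reading, freeing the participant level only, does not bring the 24-month test back to 5% when clinics differ.

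Three other inferences go too far:

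- *The 12-month test always loses nearly all its power.* That holds where 12-month retention is high. Elsewhere 18–35% remains of 80%, and more in the extreme case.
- *The permitted transformation is useless.* It narrows the distortion clearly.
- *The interaction must not be interpreted.* A widening gap in days is a true difference in days in care, and whether to interpret it is a preference.

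Finally, the larger 24-month figures depend on assumed differences between clinics in retention. Without them the error is about 10–13%.

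**Conclusion.** The point holds in conditional form. It is certain from the article that retention is one count truncated at two horizons and that it is sent, without exception, to the linear model used for the scale scores. With random intercepts, a common residual variance and raw days, the 24-month test runs at about 10–18% instead of 5%. The 12-month test almost never rejects under the null and loses more than half its power over assumed retention from 95/90% to 50/25%. These sizes rest on assumed retention curves and, for the upper part of the range, on assumed clinic differences. One of six primary outcomes is affected. Neither the transformation clause nor a freer participant covariance alone restores the stated level, so retention should get its own specification before analysis.

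**What to change.** Take retention out of the common HLM. Compare days in care separately at 365 and at 730 days, each with its own clinic-adjusted standard error, or compare restricted mean time in care at each horizon with allowance for clinic clustering. If one model is kept, state that variances may differ by time at both clinic and participant level. Report intervention*time for retention with a note that a day difference can widen from the longer window alone.

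The cost is a sentence in the analysis plan and a separate model for one outcome; no new data are needed. The 24-month standard error will be wider, by about 30–45% in the simulations. With 35% out of care by month 24 at a constant hazard, for example, the true value was 36.6 days against 25.9 from the model (36.6/25.9 = 1.41). The 12-month standard error in that example falls from 25.9 to 13.2 days.

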### Randomization

The 21 participating clinics will first be divided into two groups based on the poverty level of the catchment area and expected enrollment of individuals with FEP for each clinic. The largest site will be matched with two clinics of a similar poverty level and clinic size as well, as noted above. The matching will be done based on a visual inspection of a scatter plot of expected enrollment by the income of each site. Then, blocks of size 2, and one block of size 3, will be randomly generated. Randomization will be performed using a randomization scheme generated by SAS 9.4. This procedure will entail (1) generating a random number 0 or 1 ten times, and (2) assigning 0 to the Usual FEP care clinic and 1 to the OTCH clinic in each matched pair. For the block of size 3, two sites will be assigned to either OTCH or Usual FEP care, and the remaining site to either OTCH or Usual FEP care as well. The statistician will notify the contact-PI once the randomization is done, and he will then call the CMHC Director to inform him/her of the assigned treatment status, followed by a written note to the Director with the same information. The random allocation within blocks of two will enable us to bring into the study one OTCH and one Usual FEP Care CMHC per month. We note that the randomization (and notification) will be done at the start of the project, which will enable us to select equal numbers of OTCH and Usual FEP Care CMHCs for data collection (at organizational, provider, and participant level) during the preparatory phase.

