After a site enters the study, the participating clinic will be asked to refer all individuals with FEP to our study team. A health provider in each of the participating clinics will be designated to be the local point person for the coordination of recruitment and follow-up of study participants in his/her site; this role will be referred to as “Local Coordinator.” As noted previously, an FEP registry is in place in Chile to identify individuals with an FEP to ensure they receive timely and appropriate treatment. The Local Coordinators can use that database to identify potential participants at their clinics. Using this tool, the Local Coordinator will assign a numeric screening ID number to each potential participant and maintain a log with this information in a secure cabinet in each site. Each site will be assigned a numeric range (1000s, 2000s, 3000s, etc.). The Local Coordinator, who is not part of the OTCH research team, will contact the potential participants by phone, videoconference, or in-person when possible. If verbal consent is obtained, the Local Coordinator proceeds with a brief introduction to study. The Local Coordinator will briefly explain that he or she can participate in a research study and will describe the study’s purpose. If the client accepts to participate, the Local Coordinator will notify a member of the Research Team, known as the Registration Designee, who will oversee assessing the capacity of consent and administering the informed consent form. If someone serves as a Registration Designee for the participant, this person will not be allowed to serve as an interviewer for this participant in order to maintain the blind. This process will take place remotely unless the clinic is open for in-person appointments. Once consent is obtained, an interviewer will be notified so he/she can contact the potential participant and conduct the baseline assessment. Similar procedures will be followed for minors, and for providers, policy makers, health directors, and family members who participate in the study.

Following the recommendations by McRae et al. [17] and Giraudeau et al. [18] on administering consent forms in cluster RCTs, there will be two different consent forms: one for participants from intervention clinics and another one for participants from controls clinics. In addition, we will have other consent forms for policy makers, health directors, providers, and family members.

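### For the four primary outcomes with a scheduled baseline, the Aim 1a model leaves the baseline score out; it also omits the matching variables and ties adjustment to observed imbalance

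*Protocol article*

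**What the plan says.** The section on Aim 1a and 1b analyses tests each of six primary outcomes in a hierarchical linear model with clinic and participant random effects. The named fixed effects are arm, "time (12 or 24 months), and intervention*time". Baseline is not a level of time. The Aim 2a model for the secondary clinical outcomes does include baseline as a time level.

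On covariates, the Aim 1a text says only: "If descriptive analyses identify any baseline differences between randomized groups of participants at baseline, we will consider adding the respective covariate". It names no covariate and no threshold.

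Table 4 schedules a baseline for acceptability (EBPAS), uptake (CollaboRATE, SDM-Q-Doc, RSA and the service-receipt questions), patient-centeredness (YSS) and adherence (BARS). Fidelity is scheduled at 6, 12 and 24 months. Retention counts days from randomization.

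Under Randomization, the clinics are "divided into two groups based on the poverty level of the catchment area and expected enrollment", and allocation is made within matched blocks. Neither variable, nor the block, is among the Aim 1a fixed effects. Poverty and participant baseline factors enter only as moderators in Aim 1b.

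**The concern.** In a trial with 21 clinics, precision is scarce. A baseline measure of the outcome is usually the best available predictor of its follow-up value, and here it is collected and left unused for the primary contrasts. The matching variables were presumably chosen because they are expected to matter. The Aim 1b text also expects poverty and baseline participant characteristics to be related to service and implementation outcomes.

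A rule that adjusts only after a difference is seen has two weaknesses. A covariate improves precision through its correlation with the outcome, not through its observed imbalance, so the trigger looks at the wrong quantity. And a commitment only to consider adjustment leaves the final model undecided once baseline data are in hand.

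Recruitment adds to this. Clinics are told their allocation at the start of the project, and clinic staff identify participants afterwards: "The Local Coordinators can use that database to identify potential participants at their clinics". Differences between arms at baseline can therefore arise from recruitment as well as from chance.

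**Working it through.** **Inputs from the protocol (Sample size and power analysis).** "We also assume an alpha of 0.05 and that all tests are 2-tailed". The target is "80% power to detect a difference in mean outcomes between study conditions with a moderate effect size of Cohen’s *d* = 0.35". The sample is stated as follows: "power was calculated conservatively based on the participation of 270 participants", "anticipating a possible participant drop-out of ~10"%. The ICC is 0.05 and there are 21 clinics, taken as 10.5 per arm and 135 participants per arm.

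**Assumed.** The protocol gives no correlation r between baseline and follow-up score. I take 0.3 to 0.5, acting on within-clinic variance only. It also does not say what share of between-clinic variance the matching variables explain, so I put no figure on their contribution.

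**Step 1: the plan's own figure.** Cluster size is 270/21 = 12.86. The design effect is 1 + 11.86 × 0.05 = 1.593. The variance of the difference, in SD units, is 4 × 1.593/270 = 0.0236, so SE = 0.1536. Power at d = 0.35 is Φ(0.35/0.1536 − 1.96) = Φ(0.318) = 62.5%, and the detectable d is 2.802 × 0.1536 = 0.43. The stated 80% is not reproduced. That is a separate issue; 62.5% serves here only as the unadjusted reference.

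**Step 2: add the baseline score.** Var = 2 × 0.05/10.5 + 2 × 0.95 × (1 − r²)/135. The first term is 0.00952 throughout. This is a comparison of means at a single follow-up, as in the plan's own calculation. The t columns use the non-central t distribution: 19 df without clinic covariates, 17 df with the two matching variables.

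| r | Within-clinic term | SE | Power, normal | Detectable d, normal | Power, t |
|---|---|---|---|---|---|
| 0 (unadjusted) | 0.01407 | 0.1536 | 62.5% | 0.43 | 58.0% (19 df) |
| 0.3 | 0.01281 | 0.1494 | 64.9% | 0.42 | 59.8% (17 df) |
| 0.5 | 0.01056 | 0.1417 | 69.5% | 0.40 | 64.4% (17 df) |

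The t column charges two df for the matching variables but credits them with no explained variance. If the baseline score also explains between-clinic variance to the same degree, the normal-approximation figures become 66.6% (r = 0.3) and 74.9% (r = 0.5). Reaching 80% would need r of about 0.58 at both levels.

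**Step 3: what the conditional rule achieves.** Three rules were simulated on clinic means (21 clinics, 13 participants each, ICC 0.05, 20,000 runs). The trigger was taken as a baseline difference with p < 0.05, because the protocol gives none. Adjustment here is on clinic means, so the levels are not comparable with the table above; the comparison between rules is what matters.

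| | Never adjust | Adjust if baseline p < 0.05 | Always adjust |
|---|---|---|---|
| Power at d = 0.35, r = 0.5 | 57.9% | 57.9% | 67.9% |
| Power at d = 0.35, r = 0.7 | 58.1% | 59.2% | 83.7% |

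Type I error under the conditional rule was 4.6% (r = 0.5) and 3.7% (r = 0.7).

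**The case against.** **Choosing a model after seeing data inflates the 5% error rate.** A reader might infer this, but the protocol does not support it. The trigger is a descriptive look at baseline, not at outcomes, and the simulated rule is conservative. Inflation, to 7.6% to 8.3% in the same simulation, appears only if the analyst reports whichever analysis is significant. The protocol does not say that this will be done. What stands is that the wording leaves the model open.

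**The whole primary family loses its baseline.** It does not. Fidelity has no baseline in Table 4, and retention cannot have one. EBPAS and SDM-Q-Doc, and the provider version of the RSA, are provider measures. The power figures rest on 135 participants per arm and do not apply to them.

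**Adjustment would cure recruitment bias.** Clinics are asked to refer everyone with FEP, so selective recruitment is possible rather than shown. Covariates handle only the measured part of any imbalance.

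**This is analysis-plan detail.** The text speaks of the primary fixed effects, which leaves room for others, and a condensed article need not list every covariate. That is fair for a full covariate list: adding age, sex or PANSS would be a matter of preference. It does not cover the conditional rule, which the article states, or the restriction of time to 12 and 24 months, which contrasts with Aim 2a.

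**Adjustment can do harm.** OTCH teams have a three-month training period before implementation, and the article does not say whether provider baselines come first. If they do not, adjusting for them could remove part of the effect. This stands and limits the fix.

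**Conclusion.** The point holds for the four primary outcomes with a scheduled baseline as regards the unused baseline score, and for all six as regards the matching variables. The stated rule gives up nearly all the precision that prespecified adjustment would bring and leaves the model undecided after baseline data are seen.

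For participant-level outcomes the gain at d = 0.35 is about 2 to 6 percentage points on clinic df (58% to between 60% and 64%), or about 2 to 7 points by normal approximation (62.5% to between 64.9% and 69.5%). It rests on an assumed r of 0.3 to 0.5 within clinics. The gain is modest and does not restore 80% power under these assumptions. It is worth having because the data are already scheduled for collection.

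**What to change.** In the Aim 1a text, delete the sentence that makes adjustment depend on observed baseline differences. In its place, prespecify:

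- for each outcome with a scheduled baseline, its baseline value as a covariate; for provider scales, only if that baseline is measured before OTCH training, and the text should say whether it is;
- for all six outcomes, clinic poverty level and expected enrollment as fixed covariates;
- a test of arm on clinic-level degrees of freedom.

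This needs wording only, since the variables are already collected or were used for matching. The price is two clinic-level df. If the matching variables explained nothing, unadjusted power at d = 0.35 would fall from 58.0% (19 df) to 57.5% (17 df). The power statement should be corrected separately, not treated as repaired by this change.
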